### **11.1 SAMPLE SIZE CALCULATIONS (CO-PRIMARY ENDPOINT – DISTANT METASTASES FREE SURVIVAL (DMFS) AND RELAPSE FREE SURVIVAL (RFS))**

The study design is a non-inferiority trial investigating whether short-term adjuvant immunotherapy, is non-inferior to long-term adjuvant immunotherapy (standard of care) with a non-inferiority margin (4.0%) being accepted as being clinically appropriate in this study population.

Assumptions for the sample size calculation:

- DMFS at 2 years was 88.1% for stage IIb-c patients (Keynote 716 study) (1)
- DMFS at 2 years was 70% for stage III-IV patients (Checkmate 238 trial) (2)
- DMFS for the sample size will be based on these two measurements with a conservative estimate of 75.0% at 2 years and assuming same rates for RFS.
- Power = 80%
- Alpha level = 5%
- Non-inferiority Margin = 4%
- Accrual time = 48 months
- Follow up time = 60 months

Assuming a 4-year accrual and 5-year follow-up duration, a sample size of 1872 patients (936 in each study arm) will have 80% power (90% for each endpoint, which corresponds to a total power of 81%) with one-sided 95% confidence to declare non-inferiority with a margin of 4.0% (i.e., from 75% to 71.0% in the observation group) based on a 1:1 randomization with a corresponding HR of

1.19. The sample size may be either re-estimated or the non-inferiority boundary adjusted if the number of patients lost to follow-up is of concern.

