## 9 EVALUATIONS

### 9.1 PRIMARY ENDPOINTS

The primary endpoints of the study are DMFS and RFS at 2 years.

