## 9.2 SECONDARY ENDPOINTS

The secondary endpoints are long-term DMFS, RFS and OS. DMFS and RFS are evaluated with radiology and clinically. OS is evaluated based on survival data in patient medical records. For the secondary endpoints, the patients will be followed for OS for at least five years.

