## 11 STATISTICAL METHODS

The efficacy analyses of DMFS and RFS will include all per-protocol patients (intention-to-treat population for sensitivity analysis). DMFS is defined as the time from start of treatment to detection

of distant relapse or death and RFS as the time from start of treatment to detection of relapse (local, regional or distant) or death. Kaplan-Meier techniques will be used to plot both outcomes. Comparison of outcomes between the study arms will be based on a Cox regression model. The hazard ratio (HR) associated with the study arms will be derived from this model along with the associated 95% confidence interval (CI). A Cox regression model with intervention as the exposure and the co-primary endpoints and adjusted for the tumour stage and neoadjuvant treatment (stratification variables) will be used to assess the effect. A detailed description of the Cox regression model will be specified in the Statistical Analysis Plan (SAP). The p value for testing the null hypothesis that the HR between the interventions will be greater than or equal to 1.19 will be derived from this model by comparing the log-likelihood of the fitted model with the log-likelihood of a model where the HR between the groups is set to 1.19 by use of a likelihood ratio test.

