| CT scan thorax-abdomen-brain/MRI brain or i.v. contrast enhanced whole body FDG-PET-CT including brain or whole body FDG-PET-CT + MRI brain (e) | X (f)                                                                                 |                                                                             | X                                    |                                       |                                       | X                                     |                                       |                                       |                                       |                                       |
| Overall survival follow-up                                                                                                                      |                                                                                       |                                                                             |                                      |                                       |                                       |                                       |                                       |                                       | X                                     | X                                     |
| SAE                                                                                                                                             |                                                                                       | X (h)                                                                       | X (h)                                | X (h)                                 | X (h)                                 |                                       |                                       |                                       |                                       |                                       |

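### The stated 90% power per endpoint needs 5 to 9 years of follow-up per patient, but the primary endpoints are set at 2 years, where power is about 57–80% depending on an unstated data cut

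*Protocol*

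**What the plan says.** Protocol section 9.1 reads: "The primary endpoints of the study are DMFS and RFS at 2 years". The Synopsis and section 5 (Aim and hypothesis) say the same. Section 9.2 reads: "The secondary endpoints are long-term DMFS, RFS and OS".

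Section 11.1 fixes both the control rate and the margin at 2 years. The rate is "a conservative estimate of 75.0% at 2 years and assuming same rates for RFS" and the margin is a "margin of 4.0% (i.e., from 75% to 71.0% in the observation group", converted to a hazard ratio of 1.19. The power statement then uses a different horizon: "Assuming a 4-year accrual and 5-year follow-up duration, a sample size of 1872 patients (936 in each study arm) will have 80% power", "with one-sided 95% confidence to declare non-inferiority", with 90% per endpoint and 81% in total.

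Section 11 defines DMFS and RFS as times from treatment start to event, with no truncation. It tests "the null hypothesis that the HR between the interventions will be greater than or equal to 1.19" in a Cox model and leaves the model's details to the SAP. It names neither a data cut nor the time of the primary analysis. Section 11.3 raises the sample size to 1,880 and sets the final alpha at 0.045.

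**The concern.** The event count behind the power claim belongs to the long-term DMFS and RFS that section 9.2 calls secondary. The primary endpoints stop at 2 years, when far fewer events will have occurred. Non-inferiority power depends on the number of events, so the stated figure may not apply to the endpoint it is attached to.

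The stake is a false negative. Section 11.2 tests DMFS first and goes on to RFS only if DMFS succeeds. If DMFS is underpowered, a 6-month arm that is truly equivalent could fail at the first step, after 1,880 patients have been enrolled.

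This cannot be left wholly to the SAP, because the endpoint time and the power claim are both fixed in the protocol. A SAP that cuts at 2 years makes the stated power wrong. A SAP that uses all follow-up turns a secondary endpoint into the primary one.

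**Working it through.** **Inputs, all from the protocol.** Event-free rate 75% at 2 years, the same for DMFS and RFS (11.1). Margin 75% to 71%, HR 1.19 (11, 11.1). One-sided 5% (11.1), final alpha 0.045 (11.3). 1:1 allocation, 48 months' accrual, 60 months' follow-up (11.1). N = 1,872, or 1,880 with the interim analysis (11.1, 11.3). Total duration about nine years (Synopsis), so the 5 years run after the 4-year accrual.

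**Assumptions added here.** Exponential survival, uniform accrual, truly equal arms, no loss to follow-up.

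**Margin.** ln(0.71)/ln(0.75) = 1.1905, which agrees with 1.19. ln(1.19) = 0.1740.

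**Hazard.** λ = −ln(0.75)/2 = 0.1438 per year.

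**Event probability** when follow-up is uniform between a and b years: 1 − (e^(−λa) − e^(−λb)) / (λ(b − a)).
- a = 5, b = 9: 1 − (0.4871 − 0.2740)/0.5754 = 0.630
- a = 2, b = 6: 1 − (0.7500 − 0.4219)/0.5754 = 0.430
- exactly 2 years for everyone: 0.250

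**Power** with d events: Φ(0.1740 × √d / 2 − z), with z = 1.645 at 0.05 and 1.695 at 0.045.

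**The plan's own figure first.** N = 1,872 over 5–9 years gives 1,872 × 0.630 ≈ 1,179 events. Then 0.1740 × √1,179 / 2 = 2.986, and Φ(2.986 − 1.645) = 91.0%. The stated 90% reproduces on this horizon.

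**The same formula at N = 1,880:**

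| Data used | Events | Power, alpha 0.05 | Power, alpha 0.045 |
|---|---|---|---|
| Cox model cut at 24 months | 470 | 59.5% | 57.5% |
| All data when last patient reaches 24 months (2–6 years each) | 808 | 79.6% | 78.1% |
| Exactly 60 months per patient | 964 | 85% | 84% |
| 4-year accrual plus 5 years (5–9 years each) | 1,184 | 91.1% | 90.3% |

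**Direct 2-year difference against 4 points.** SE = √(2 × 0.75 × 0.25 / 940) = 0.01997. Power = Φ(0.04/0.01997 − 1.645) = 64.0%; at alpha 0.045 it is 62.1%.

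**Check by simulation** (4,000 trials per case, N = 1,872): 59.4% for the 24-month cut, 78.8% for 2–6 years, 91.0% for 5–9 years.

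**Events needed for 90%**: 4(z + 1.282)²/0.1740² = 1,132 at alpha 0.05 and 1,171 at alpha 0.045.

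**Patients needed for 90% per endpoint on strict 2-year data** at alpha 0.05: about 4,016 (2-year difference) to 4,532 (Cox model cut at 24 months).

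**The case against.** The strongest defence is that nothing in the protocol censors the Cox model at 24 months. Section 11 defines untruncated times to event, tests a hazard ratio and refers to the SAP for detail. On that reading, "at 2 years" only anchors the rate and margin, and the sample size was worked out for the analysis intended. This stands in part: a reader might infer that power simply is 60–64%, and the documents do not support that. It is one end of a range that reaches about 80%. The defence does not rescue the 90%, because only the long-term analysis delivers it and section 9.2 makes that secondary.

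Three other stronger readings are tempting.

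- *Late relapses are not collected.* Appendix 1 ends physical examinations at month 36 and lists only "Overall survival follow-up" at months 48 and 60. But section 16.2 requires relapses to be reported however they are found, Appendix 1 says routine national follow-up must also continue, and the section on treatment in the case of recurrence keeps patients with local recurrence under protocol follow-up for five years. What remains is narrower: no study-specific relapse assessment is scheduled after month 36.
- *Joint power is the square of the 2-year figure.* That copies the protocol's multiplication of 0.9 by 0.9. Every DMFS event is also an RFS event, so the tests are strongly correlated and the product is too low. What does follow is that joint power cannot exceed the power for DMFS alone.
- *Using all follow-up would often pass an arm that loses 4 points at 2 years.* That depends on the hazards after month 24, particularly on their becoming equal. The documents give no basis for choosing that pattern.

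**Conclusion.** The point holds as an inconsistency between the endpoint, the data cut and the power statement. It is not a calculation error, since the 90% reproduces on the horizon used. Under the protocol's own assumptions, power per endpoint is 59.5% to about 80% at alpha 0.05 on any 2-year reading, and 57.5% to 78% at the final alpha of 0.045. The stated 81% in total is also out of reach on those readings, because joint power is bounded by the single-endpoint figure, at most 79.6%.

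These figures assume exponential survival, truly equal arms and no loss. The protocol gives no dropout rate. Loss to follow-up, or exclusions from the per-protocol set that section 11 makes primary, would lower the number of events and the power. An RFS rate below 75% would add RFS events but would not help DMFS, which is tested first.

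The matter should be settled before any comparative results are seen, so that the data cut is not chosen afterwards.

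**What to change.** State one horizon and one data cut for the primary analysis, and make the Synopsis and sections 5, 9.1, 11 and 11.1 agree. Two routes do this.

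(a) Keep the 2-year primary endpoints. Restate power per endpoint in 11.1 for the chosen cut: about 57–64% for a strict 24-month analysis, or about 78–80% for all data when the last patient reaches 24 months. Keep the long-term Cox analysis secondary. The cost is wording and a less favourable stated power.

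(b) Make the long-term Cox analysis primary. Remove the 2-year qualifier from the primary endpoints, set the data cut at about 1,170 DMFS events (90% at alpha 0.045), and record relapse status, date and site at the existing 48- and 60-month contacts. The cost is a few data items at two contacts. Two cautions apply. The target is about 99% of the 1,184 events expected with no loss (1,171/1,184), so there is almost no slack. It also needs events beyond month 60 from early enrollees: if relapse data stop at month 60 for each patient, about 964 events and 84–85% power are expected. Section 11.1 should say which applies.

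Neither route adds patients. Restoring 90% on strict 2-year data would take about 4,000 to 4,500 patients.

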## 2. Safety monitoring

- a. SAE:s and SUSAR:s
- b. New information that has been published if applicable
- c. The results of the interim analysis (done when approximately two-thirds of the total number of planned subjects are enrolled)

However, the DSMB may for any concerns regarding safety recommend stopping the trial.

It is the responsibility of the Sponsor, based on the advice provided by the DSMB, to decide whether a premature end of the study will be made.

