## **Attendance**

At least one of the independent members should attend the official DSMB meeting.

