## **Meeting preparation and plan**

- Investigator(s) is responsible to collect all relevant information and safety data, and submit the data to Sponsor.
- The Sponsor or project manager distributes the prepared material (as described under DSMB review) to DSMB members 1 (one) week prior to the meeting, and calls for a meeting.
- DSMB members meet on-line, by telephone or in person and discuss the data, meeting minutes will be written and filed.
- A recommendation to continue or stop the trial will be made during or after the meeting by the independent DSMB members.

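### Section 11.1 lets the non-inferiority margin be changed for loss to follow-up, which contradicts its own clinical justification and the fixed HR of 1.19 in Section 11

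*Protocol*

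**What the plan says.** Section 11.1 sets the margin at 4 percentage points at 2 years, from 75% to 71%, with a corresponding hazard ratio (HR) of 1.19. It describes this as a "non-inferiority margin (4.0%) being accepted as being clinically appropriate in this study population". The control rate is a "conservative estimate of 75.0% at 2 years and assuming same rates for RFS". The section closes with a permission: "The sample size may be either re-estimated or the non-inferiority boundary adjusted if the number of patients lost to follow-up is of concern".

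Section 11 specifies the test. The fitted Cox model is compared with "a model where the HR between the groups is set to 1.19 by use of a likelihood ratio test". No alternative null value is foreseen there.

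Section 11.2 presents hierarchical testing of DMFS and then RFS as preserving the overall type I error rate. Section 11.3 places an interim analysis when about two-thirds of the planned subjects are enrolled. Neither says what happens if the boundary changes. Section 15.3 requires ethical and/or regulatory approval for substantial modifications in general, without mentioning the margin.

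**The concern.** A non-inferiority margin is a judgement about how much efficacy may be given up. The protocol makes that judgement on clinical grounds for this population. The number of patients lost to follow-up is a matter of study conduct and carries no information about what deficit patients should accept. Section 11.1 nevertheless offers a change of boundary as an alternative to changing the sample size.

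The text also conflicts with itself. A null hypothesis fixed at HR 1.19 in Section 11 and a movable boundary in Section 11.1 cannot both stand. What is at stake is the meaning of a positive result. If the boundary is widened, a declaration of non-inferiority no longer excludes a 4-point deficit at the stated error rate, although 4 points is the only deficit the protocol justifies.

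**Working it through.** **Inputs from the protocol.** Control rate 75% at 2 years, margin 4 points, one-sided 5%, 90% power per endpoint, 1:1 allocation, 4-year accrual, 5-year follow-up (Section 11.1); 1,872 patients before and 1,880 after allowing for the interim analysis (Sections 11.1 and 11.3).

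**Assumptions added here.** Exponential event times, uniform accrual, 5 years of follow-up after accrual closes, a true HR of 1 for power, and event losses of 10%, 20% and 30%. The protocol gives no loss rate and no size of adjustment.

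**Step 1: the plan's own figures.**
- Margin as HR: ln(0.71)/ln(0.75) = 1.1905, which agrees with 1.19.
- Yearly hazard: λ = −ln(0.75)/2 = 0.1438.
- Event probability: 1 − [exp(−5λ) − exp(−9λ)]/(4λ) = 0.6296. This gives about 1,179 events from 1,872 patients and 1,184 from 1,880.
- Power: Φ(ln(1.1905)·√D/2 − 1.645) = 91.1% at D = 1,179 and 91.2% at D = 1,184. The protocol states 90%, so its figure is reproduced closely. The joint figure is 0.9 × 0.9 = 81%.

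**Step 2: loss to follow-up with the margin held at HR 1.1905.** The same formula is used with D = 1,184 × (1 − loss).

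**Step 3: loss to follow-up with the boundary widened only enough to restore 90% power.**
- New boundary: HR_new = exp[2(1.645 + 1.282)/√D].
- New margin in points: 75 − 100 × 0.75^HR_new.
- Chance of declaring non-inferiority when the true HR is 1.1905: Φ[(ln HR_new − ln 1.1905)·√D/2 − 1.645].

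| Event loss (assumed) | Events | Power, margin fixed | HR restoring 90% | Margin, points | False-claim rate at a true 4-point deficit |
|---|---|---|---|---|---|
| 10% | 1,065 | 88.5% | 1.196 | 4.1 | 5.9% |
| 20% | 947 | 85.0% | 1.209 | 4.4 | 8.1% |
| 30% | 829 | 80.6% | 1.225 | 4.7 | 11.0% |

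With the margin fixed, the last column stays at 5% in every row.

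**Step 4: sensitivity to the starting point.** Starting instead from 1,127 events, the number that gives exactly 90% power, the same losses give false-claim rates of 6.7%, 9.1% and 12.2%. The margins are then 4.2, 4.5 and 4.8 points. Power with the margin fixed is 87.1%, 83.5% and 78.9%. The conclusion does not change.

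**The case against.** The strongest defence is that the stated trigger is a count of patients lost, not the treatment effect. If the change were made blind to outcome, a 5% test of the new margin would keep 5% error at that new margin. This stands, so it would be too strong to say that type I error control is removed altogether. What is lost is control against the 4-point margin, and only if the boundary is widened. The text names no direction, but narrowing would make the precision problem worse. Blinding is not required either.

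A second defence is that Section 15.3 would probably require approval for such a change, so the sponsor could not simply act alone. That is likely, but it is a general approval rule. It neither fixes the margin nor protects a claim made against 4 points.

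A reader might also infer much larger error rates. Moving the boundary to 5 or 6 points (HR 1.24 or 1.29) with 1,184 events gives 17% or 40%. The formula does yield those values, but 1,184 is the event count with nobody lost, which does not fit a trigger based on loss. The protocol names neither boundary. If widening only restores 90% power, 5 points corresponds to about 741 events (37% of events lost) and 14%, and 6 points to about 529 events (55% lost) and 23%.

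Finally, a reader might connect the clause to the DSMB charter in Appendix 2. There the sponsor or project manager distributes the DSMB material, which includes the interim results, and one independent member suffices for attendance. No section says who may change the margin or that this person would have seen the interim HR. Attendance has no bearing on the margin. Those are questions of DSMB independence and form no part of this point.

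**Conclusion.** The point holds as a contradiction within the protocol and as a poorly chosen permission. Section 11.1 permits an unbounded change to a margin that the same section justifies clinically and that Section 11 fixes at HR 1.19, and no other section withdraws or limits that permission. Under the assumptions above, restrained use would raise the false-claim rate against the 4-point margin from 5% to between about 6% and 11% for event losses of 10% to 30%; larger changes would raise it further. The permission has not been exercised, and these sizes are illustrations of what the text allows. Leaving the margin alone costs only power, down to about 81% per endpoint at 30% loss, so the permission gives up the meaning of the claim to address a modest loss of power.

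**What to change.** In the last sentence of Section 11.1, delete the alternative that allows the boundary to be adjusted. Add that the margin of 4 points (HR 1.19) is fixed for the whole trial, consistent with Section 11. Limit the response to loss to follow-up to three options: sample size or event re-estimation from blinded pooled data, longer follow-up, or accepting the loss and restating the lower power.

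The edit costs one clause and adds no patients in itself. If re-estimation is later used, the number follows from 1,880/(1 − loss): about 2,089 at 10% loss and 2,350 at 20% (assumed rates). Section 11.1 already allows that route.

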## 11.2 CO-PRIMARY ENDPOINTS

Distant metastatic free survival and RFS are co-primary endpoints and to preserve the overall type I error rate, comparisons will be performed according to the following hierarchical testing:

- 1) The alternative non-inferiority hypothesis,  $H_{11}$ : DMFS short-term treatment is not inferior to long-term treatment (standard of care) for the first co-primary endpoint (DMFS). If  $H_{11}$  is accepted, i.e., non-inferiority is declared in (1), then the following hypothesis will be tested.
- 2) The alternative non-inferiority hypothesis,  $H_{12}$ : DMFS short-term treatment is not inferior to long-term treatment (standard of care) for the second co-primary endpoint (RFS).

Each test will be performed at the 5% level of significance, with comparisons in the sequential testing procedure being conditional on the rejection of the null hypothesis of the previous comparison.

## 11.3 INTERIM ANALYSIS

If we allocate  $\alpha = 0.005$  to the interim analysis and  $\alpha = 0.045$  to the final analysis then the total sample size would increase from 1872 to 1880 subjects (940 in each arm). The calculation was made using the O'Brien-Fleming Boundary. The interim analysis will be conducted when approximately two-thirds of the total number of planned subjects are enrolled which is the optimal timing when using the O'Brien-Fleming Boundary for both co-primary endpoints (12). The results of the interim analysis will be carefully assessed by the Data safety monitoring board (DSMB) without delay and in the case of inferiority of the experimental arm the study will be prematurely terminated and all sites informed.

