## 6 EVALUATION OF RISK AND BENEFIT

With the adjuvant standard treatment today for patients with high-risk CMM, the number needed to treat (NNT) to prevent relapse is roughly seven while adverse reactions grade III-IV develop in around 1/7 patients. This means that the likelihood of benefit equals the risk for developing severe side effects.

If the results show that a shorter treatment period is as effective as the current one-year scheme it would greatly benefit the patients by decreasing the risk for side effects and by reducing the number of hospital visits. In addition, the health care resources saved would enable spending more resources in other areas. The Swedish Melanoma Patient Group (Melanomföreningen) has been addressed and they are in favor of the study, although they anticipate that patients might not want to participate due to fear of receiving an inferior treatment. However, none of the registration studies have so far shown that adjuvant systemic therapy in CMM patients significantly prolongs overall survival (OS)

and its routine use is based on prolonged RFS. As in other malignancies, adjuvant treatment for CMM is most often given in vain as many patients would not relapse even without adjuvant treatment and a large group of patients relapses despite having received adjuvant treatment. Complete response is achieved in around 20 % of metastatic CMM patients and these responses are usually long lasting. This raises the question whether it might be better to refrain from adjuvant immunotherapy and instead save this treatment for those patients who relapse with advanced disease. The patients in whom we prevent relapse by adjuvant immunotherapy may be the same patients who gain from immunotherapy with complete response in the advanced setting. In addition, a recent cohort study did not indicate any OS benefit after the introduction of immunotherapy (11). Importantly, an interim analysis will be conducted to ensure that the experimental arm (6 months of treatment) is not clearly inferior to the standard treatment period of 12 months, in which case the trial recruitment will be halted. Noteworthy, similar studies have been conducted in breast and colorectal cancer patients where adjuvant treatment significantly prolongs OS.

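### Two-thirds enrolment is not two-thirds of the information: the interim falls at about 18% to 43% of events, the 0.005/0.045 split is not O'Brien-Fleming there, and the inferiority look is weak

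*Protocol*

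**What the plan says.** Section 11.3 sets the trigger: "The interim analysis will be conducted when approximately two-thirds of the total number of planned subjects are enrolled". It presents that moment as the optimal one for an O'Brien-Fleming boundary on both co-primary endpoints. It allocates alpha of 0.005 to the interim and 0.045 to the final analysis, raises the total from 1872 to 1880, and adds: "The calculation was made using the O'Brien-Fleming Boundary". No event count or information fraction is given.

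On the action, section 11.3 says "in the case of inferiority of the experimental arm the study will be prematurely terminated and all sites informed". Section 6 offers the look as a protection for patients: "an interim analysis will be conducted to ensure that the experimental arm (6 months of treatment) is not clearly inferior", and gives the consequence as "in which case the trial recruitment will be halted". The DSMB charter (Appendix 2, DSMB review) names inferiority at the interim, or safety, as the grounds for stopping. No section describes an early claim of non-inferiority.

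Section 11 specifies a Cox model with a hazard-ratio margin of 1.19. Section 11.1 works with one-sided 95% confidence. Section 11.2 puts each test in the hierarchy at 5%.

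**The concern.** An O'Brien-Fleming boundary is indexed by the fraction of statistical information available at the look. In a time-to-event comparison that fraction is the share of events. Patients enrolled shortly before the interim have contributed almost no follow-up, so the share of events lags far behind the share enrolled.

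Three things are at stake. The timing claim and alpha levels in 11.3 do not correspond to the boundary they are said to come from. The look that section 6 relies on to protect patients in the 6-month arm may have little ability to detect inferiority, and nothing tells the DSMB so. And alpha is set aside from the non-inferiority test for a look whose only described efficacy outcome is a stop for inferiority.

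**Working it through.** **Inputs.** From section 11.1: 75% event-free at 2 years for both endpoints, 4-year accrual, 5-year follow-up, one-sided 5%, 90% power per endpoint, HR margin 1.19. From section 11.3: N = 1880, look at two-thirds enrolled. Assumed here: constant hazard, uniform accrual (1880/4 = 470 a year), no dropout, equal hazards.

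**The plan's own figure.** Hazard λ = −ln(0.75)/2 = 0.1438 per year. With analysis at year 9, the event probability is 1 − [exp(−5λ) − exp(−9λ)]/(4λ) = 0.630. So 1872 patients give 1,179 events, and power is Φ(ln(1.19)·√1179/2 − 1.645) = Φ(1.34) = 91%, close to the stated 90%. About 1,132 events are needed for exactly 90%. For N = 1880 the year-9 count is 1,184.

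**Events at the interim.** Two-thirds of 1880 is 1,253 patients, reached at 2.667 years (month 32). Event probability: 1 − (1 − exp(−2.667λ))/(2.667λ) = 0.169. Events: 1,253 × 0.169 = 212.

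**Information fraction.**
- Against year 9: 212/1,184 = 18% (19% of the 1,132 needed).
- Follow-up cut at 2 years per patient, since section 9.1 names the endpoints at 2 years: interim events 470 × [0.667 × 0.25 + (2 − 0.25/0.1438)] = 201; final events 1880 × 0.25 = 470; fraction 43%.
- Other readings of the final date lie between: 22% for a fixed 5 years per patient, 26% for 2 years after last entry, 33% for 1 year after last entry.
- A true two-thirds of events would arrive about year 5.7 (of 1,132) to 5.9 (of 1,184), after the 4-year accrual has ended.

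**O'Brien-Fleming levels, one-sided 5%.** With Lan-DeMets spending, the interim level at fraction t is 2[1 − Φ(1.96/√t)].

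| t | Interim level |
|---|---|
| 0.18 | 0.000004 |
| 0.43 | 0.003 |
| 0.667 | 0.016 (classic two-look form 0.018, final 0.044) |

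A level of 0.005 corresponds to about half the information (t = 0.49), which is none of these.

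**Strength of the inferiority look.** With 212 events, SE(ln HR) = 2/√212 = 0.137. Section 11.3 does not say which null 0.005 refers to. Against HR 1, the observed HR must exceed exp(2.576 × 0.137) = 1.42. The chance of crossing is 1 − Φ(2.576 − ln(HR)/0.137):

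| True HR | Chance of stopping |
|---|---|
| 1.19 | 10% |
| 1.3 | 25% |
| 1.4 | 45% |

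Against HR 1.19 the threshold would be 1.19 × 1.42 = 1.69.

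**Cost of the withheld alpha.** If the final test is run at a nominal 0.045 rather than 0.05, power is 90.3% versus 91.1% at 1,184 events, and 57.5% versus 59.5% at 470 events. The loss is 0.8 to 2 points, in the conservative direction.

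**What 0.045 means.** A final test at nominal 0.045 with 90% power would need, by ratio, 1872 × [(1.695 + 1.282)/(1.645 + 1.282)]² ≈ 1,937 patients (about 1,930 if an early non-inferiority crossing also counts). Spending 0.005 first with 0.05 in total needs about 1,888 at 43% information, 1,883 at 50% and 1,876 at two-thirds, with nominal final levels of 0.048 to 0.049. The stated 1880 fits that second reading.

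**The case against.** The best defence is that an enrolment trigger is sensible for a harm look: section 6 wants recruitment halted if the short arm is clearly worse, and a look at two-thirds of events would come too late for that. This stands as an argument for an early look. It does not support calling the timing optimal for O'Brien-Fleming, nor the 0.005/0.045 levels.

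Several stronger readings are tempting and are not supported:

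- A reader might take 18% as the fraction. The protocol states no planned number of events and does not fix the date of the primary analysis, so the supportable range is 18% to 43%.
- A reader might infer that the final test is run at a needlessly strict 0.045. Section 11.3 speaks of allocating alpha, and the increase of only 8 patients fits cumulative spending with a nominal final level near 0.048 to 0.049. What the text does leave unresolved is 0.045 in 11.3 beside 5% per test in 11.2.
- A reader might discount all events in the first 6 months because the arms are treated alike. Section 8.2 gives neoadjuvant patients in the short arm four months after surgery, and their share is not stated, so no such discount is applied here.
- A reader might infer that moving to an O'Brien-Fleming boundary at the true fraction repairs the look. At 18% it would need an observed HR near 1.85 and would cross about 0.1% of the time at a true HR of 1.19 and 2% at 1.4, well below the present rule.

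It is also fair that boundary details and the tested hypothesis may sit in an analysis plan that is not shown. The point therefore rests on what 11.3 itself asserts. Lastly, terminating a study includes halting its recruitment, so the difference between sections 6 and 11.3 is minor, though the two are not the same consequence.

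**Conclusion.** The concern holds. Section 11.3 equates two-thirds enrolment with two-thirds information, and none of the readings of the final analysis examined comes near that: the range is 18% to 43%, given 75% at 2 years with constant hazard, uniform accrual and no dropout. The 0.005/0.045 split is not the one-sided 5% O'Brien-Fleming boundary at 18%, 43% or 67%.

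The main consequence is that the safeguard in section 6 is weak. If 0.005 is tested against HR 1, the look would stop the trial about one time in ten when the true HR equals the 1.19 margin, and less than half the time at 1.4.

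As described, the look can only stop for inferiority. Such a stop cannot create a false non-inferiority claim, so it needs no share of the non-inferiority alpha. Withholding it costs at most 1 to 2 points of power and does not inflate type I error; taken alone that would be minor. Sections 11.2 and 11.3 must be reconciled on the final level, and sections 6 and 11.3 on the consequence.

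**What to change.** In section 11.3:

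1. Remove the statement that two-thirds enrolment is the optimal O'Brien-Fleming timing.
2. Define the interim by a DMFS event count (about 210 if the present calendar timing is kept) and state the expected information fraction and the final analysis it refers to.
3. Label it an inferiority-only look. State the null hypothesis tested, and use a boundary suited to an early harm look rather than O'Brien-Fleming at about 18%. Report its crossing probabilities for a range of true hazard ratios, so that the DSMB knows what a result short of the boundary does and does not show.
4. Spend no non-inferiority alpha on it and keep the final test at one-sided 5%, in line with section 11.2. If an early non-inferiority claim is intended, say so and use Lan-DeMets spending at the observed event fraction.
5. Reconcile the consequence of an inferiority finding between sections 6 and 11.3.

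An event count of about 210 keeps the information the look has now; the gain is an honest information scale, a fitting boundary and disclosed sensitivity. The cost is a rewording of 11.3, with matching edits to the interim timing in the DSMB charter and to section 6, and no added patients. The drawback is that the interim date becomes event-driven and less predictable. The change should be made before any interim data are seen.
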